## Abstract

**Background:**

Setting healthy lifestyle habits during the formative years of childhood is critical as habits can track to adulthood and help prevent obesity and chronic disease risks in later life. While multicomponent interventions have been shown to be effective in changing the lifestyle behaviours of children, there is a limited understanding of the feasibility of such interventions in primary schools in Singapore. A multiphase mixed method study was conducted to develop and examine the feasibility of a theory-based multicomponent school-based intervention—Promoting hEatlthy Eating and Active Lifestyle (PEDAL).

**Methods:**

Underpinned by Kincaid’s ideation model, the PEDAL intervention was developed to increase fruit and vegetable consumption and decrease sedentary behaviours among children. This study consists of three phases. Phase 1 details the development of PEDAL, which consists of four components: (A) a series of interactive health education lessons, (B) actionable home activities to support habit formation, (C) parental/guardian engagement, and (D) optimising the school environment. In Phase 2, components A and B of PEDAL were implemented in two public, co-educational primary schools among Primary 5 students (aged 10–12 years) in Singapore. Data was collected quantitatively using questionnaires and qualitatively using focus group discussions (FGDs) with students and teachers. The feasibility dimensions of components A and B, including recruitment capability, data collection, social validity, and practicality were examined, and ideation on healthy eating and physical activity was explored. In Phase 3, the full PEDAL intervention was pilot-tested in two other public, co-education primary schools with the same target population, using a concurrent mixed method quasi-experimental study design. Feasibility dimensions and potential effectiveness of the intervention will be assessed.

**Discussion:**

This study will provide insights into the feasibility of PEDAL and inform its refinement. Findings from the pilot test will guide the planning of a larger-scale definitive trial.

**Trial registration:**

Registered with ISRCTN registry (ISRCTN16114046) on 16 October 2022.

**Supplementary Information:**

The online version contains supplementary material available at 10.1186/s40814-024-01479-3.

## Background

Adolescence, defined by WHO as ages between 10 and 19 years, is one of the most rapid, dynamic, and formative phases of human development [1]. It provides a window of opportunity for establishing healthy lifestyle habits that can track to adulthood [2, 3]. Yet, increasing evidence indicates that, globally, older children and adolescents do not meet dietary and movement behaviour (comprising physical activity, sedentary behaviour, and sleep) guidelines, thus contributing to the obesity epidemic [3, 4]. This is of concern as childhood obesity strongly predicts adult obesity and is associated with health problems such as diabetes and cardiovascular diseases [5–7]. Obese children also tend to have lower levels of self-esteem, a higher prevalence of depressive symptoms, and be socially marginalised with conditions persisting into adulthood [8, 9]. Recent evidence indicated an accelerated trend in children’s and adolescents’ BMI in parts of Asia [10]. The prevalence of overweight among children and adolescents (age 5–19 years) in Singapore stands at 22% in 2021, ranking third highest in the ASEAN region [11].

In Singapore, a significant proportion of primary school children were found not meeting healthy behaviour guidelines [12]. Many had diets that were lacking in fruits, vegetables, and whole grains while high in sodium and added sugar [12, 13]. The recent national Report Card on physical activity level among children and adolescents reported that only 44% and 41% of children and adolescents met the moderate-to-vigorous physical activity (MVPA) guidelines of at least 60 min daily and the recreational screen time guidelines of ≤120 min, respectively [14]. To improve children’s eating and movement behaviours, schools have been a popular means due to their potential for mass reach [15] and cost-effectiveness [16]. Recent evidence suggests that school-based interventions should be multicomponent to be effective in changing lifestyle behaviours. This means targeting more than one lifestyle behaviour simultaneously, plus engaging the family and providing environmental support [17–19]. This aligns with empirical evidence that lifestyle behaviours tend to cluster (e.g. the clustering of poor dietary habits and low levels of physical activity), indicating that a single behaviour change does not necessarily result in an overall healthy lifestyle [20].

While school-based lifestyle interventions with a multicomponent design have been conducted in Asia and Singapore, there is a paucity of published studies on the effectiveness of these interventions on obesity outcome measures (e.g. body mass index, waist circumference) [21–23]. Findings were also reported to be mixed [21, 22]. While some studies found substantial effects on health knowledge and lifestyle behaviours, behavioural outcomes were not often reported [21, 22]. Furthermore, as intervention effectiveness has shown to vary by context, information on the real-world adoption, implementation, and sustainability of multicomponent school-based interventions is lacking in the Asian context [21, 24]. Using a theory-based intervention and testing the programme theory will help understand probable “active ingredients” that make the intervention effective [1, 19]. Thus, a multiphase mixed method study was conducted to develop and examine the feasibility of a theory-based multicomponent school-based intervention—Promoting hEalthy Eating and Active Lifestyle (PEDAL) in Singapore. This study consists of three phases: a development phase (Phase 1) and two feasibility phases (Phases 2 and 3) as detailed in Fig. 1. Briefly, Phase 1 focused on the development of the intervention content, materials, and activities, while Phase 2 examined the feasibility of implementing the interactive health education lessons (Component A) and home activities (Component B) and explored ideation on healthy eating and physical activity. In Phase 3, a pilot study was conducted to examine the feasibility and potential effectiveness of the whole PEDAL intervention. This paper is reported according to the Standard Protocol Items: Recommendations for Interventional Trials (SPIRIT) guidelines [25] (Additional File 1). Findings from this study will provide critical information on the refinement of the intervention before the conduct of a definitive trial to determine the effectiveness of the intervention.

**Fig. 1 Fig1:**
[figure not shown]
Description of the multiphase mixed method study to develop and test the PEDAL intervention

## Methods

### Phase 1: Development of PEDAL

The specific aims of PEDAL are to increase fruit and vegetable intake, increase time spent on MVPA, and decrease sedentary time spent. PEDAL is underpinned by Kincaid’s ideation model, a metatheory of health communication that posits that successful interaction between resources, environment, and ideation factors would lead to behaviour change [26]. In this model, ideational factors are grouped into three domains: cognitive, emotional, and social determinants of behaviour, and the likelihood of practising a recommended behaviour increases when more factors from the three domains apply to an individual [27, 28].

Based on current literature and previous work by the team [19, 20, 29–31], factors that can potentially influence children’s healthy eating and activity behaviours include knowledge, home and school environment, attitudes, self-efficacy, emotional response, social norms and support, behavioural intentions, and habit strength. With this knowledge, a programme theory was developed for the intervention (Fig. 2), with four key components targeting these factors. The four components include a series of interactive health education lessons (Component A), actionable home activities to support habit formation (Component B), involving parents or guardians (Component C), and optimising the school environment to support and reinforce healthy eating and lifestyle behaviours (Component D). Details of these components are described below and summarised in Table 1.

**Fig. 2 Fig2:**
[figure not shown]
Illustration of the programme theory for the PEDAL intervention

**Table 1 Tab1:** Summary of intervention components and behaviour change techniques and constructs applied

Intervention component	Content	Behaviour change techniques (coded according to the BCTTv1 [32])	Ideational variables (constructs)
A. Interactive health education lessons	• Introduction of physically active and interactive health education lessons • Providing personalised lifestyle reports • Introducing goal setting and habit formation into the lessons	1.1 Goal setting (behaviour); 1.2 problem solving (coping planning); 1.4 action planning; 1.9 commitment; 2.2 feedback on behaviour; 4.1 instruction on how to perform a behaviour; 5.1 information about health consequences; 5.6 information about emotional consequences; 9.1 credible source	• Knowledge/skills • Attitudes • Self-efficacy • Emotional response
B. Actionable home activities and incentives to support habit formation	• Complete a variety of activities that can be repeated to support habit formation • Incentivising task completion	3.1 Social support (practical); 8.1 behavioural practice/ rehearsal; 8.3 habit formation; 10.1 material incentive (behaviour); 10.2 material reward (behaviour)	• Knowledge/skills • Attitudes • Self-efficacy
C. Parental/guardian engagement	• Engaging parents/guardians in home activities • Sharing of children’s personalised lifestyle reports with parents/guardians • Sharing of lesson materials with parents/guardians	2.2 Feedback on behaviour; 3.2 social support (practical)	• Attitudes • Social support
D. Optimise school environment	• Level-wide activities during recess to increase awareness of fruits and vegetables and ideas to break up sitting time • Working with canteen vendors on the providence and placements of cues to encourage fruit and vegetable intake.	7.1 Prompt/cues; 6.2 social comparison; 10.4 social reward	• Attitudes • Perceived norms • Emotional response • Environment support

An advisory committee comprising experienced health and education professionals from the Ministry of Education (MOE), the Health Promotion Board (HPB), the National Institute of Education, and the Saw Swee Hock School of Public Health was formed to provide guidance and input towards the development of PEDAL.

#### Component A: Interactive health education lessons

Consisting of five interactive face-to-face lessons, the PEDAL health education lessons were developed to cover topics on healthy eating, reducing sedentary behaviours, and habit formation (see link for introductory video: https://bit.ly/pedal-intro, and Table 2 for a summary of lesson topic and content). The concept of habit formation was included as increasing evidence has demonstrated that habit is a more important predictor of a behaviour (e.g. fruit and vegetable consumption) than intentions [33, 34] and the need to identify contingency plans that help support existing habits [35]. Adapting the concept from a habit-based healthy feeding intervention [36], students were taught to incorporate strategies such as goal setting, self-monitoring (through understanding triggers and circumstances), and self-efficacy in the PEDAL lessons. To help facilitate students’ goal setting, which provides a starting point for making specific behavioural changes, students received feedback on their lifestyle behaviours based on their baseline lifestyle behaviour data collected. To reduce sedentary time, health education lessons, typically conducted with seated students, were modified to incorporate standing and movement activities during lessons to break up sitting time [37]. This approach has the triple benefits of reducing students’ sitting time, teaching them the concept of reducing sedentary behaviour as well as being more interactive, to better engage the students and change their perception of health education lessons.

**Table 2 Tab2:** Topics covered in the health education lessons

Lesson	Topic	Content and activities
1	Calorie balance and nutrient density	• Educational video on energy density and portion sizes; • Interactive and active stand-up game to reinforce concepts learnt and bust diet myths Video links: https://bit.ly/pedal-caloriebalance, https://bit.ly/pedal-nutrientdensity (See Additional File 2 for snapshots of the lesson videos)
2	Habit formation	• Educational video on the habit formation concept; • Worksheets on goal setting based on class and individual feedback on diet and lifestyle; • Worksheets on setting action plans for diet and movement. Video link: https://bit.ly/pedal-habitformation (See Additional File 2 for snapshots of the lesson video)
3	Home assignment—PEDAL card	• Introduction to PEDAL card home activities to encourage repetition of healthy behaviours and the point system for completing home activities. (See Additional File 3 for snapshots of the home assignment tasks)
4	Sit less, move more	• Educational video on sedentary behaviours and the impacts on the body, and tips on how to break up long hours of sitting; • Interactive and active stand-up game to reinforce concepts learnt Video link: https://bit.ly/pedal-sitlessmovemore (See Additional File 2 for snapshots of the lesson video)
5	Coping Plans	• Educational slides to introduce coping plans • Interactive and active stand-up game to identify coping plans to overcome common barriers faced when increasing fruit and vegetable intakes and reducing sedentary behaviours; (See Additional File 2 for snapshots of the lesson slides)

#### Component B: Actionable home activities and incentives to support habit formation

Children’s automaticity or habit in behaviour often arises from the repetition of behaviours in a stable context [38]. To encourage sustained behavioural change and form habits, students were given home activities to complete. These consisted of individual-led tasks or tasks to be completed with their friends, family members, or guardians at their own pace. They aimed to develop students’ skills and self-efficacy in achieving set behavioural goals by targeting cognitive domains of knowledge and understanding and skill domains such as functional, interactive, and critical skills [39]. Examples of tasks include identifying three nutrient-dense foods, learning from parents how to prepare fruits independently, engaging in physical activity with their family, and executing the diet and movement habit plans students set for themselves. The home activities, presented on a card (PEDAL card, see Additional File 3 for snapshot), were introduced to students during the health education lessons, and students were given at least 6 weeks to complete the activities.

Students were encouraged to complete and repeat these activities through the collection of points. They were awarded a badge of honour (Bronze, Silver, Gold) by the end of the intervention through the accumulation of a certain number of points. Previous fruit and vegetable intervention studies have demonstrated that using small incentives is an effective way to encourage children to eat fruits and vegetables, and these induced changes persisted (at least 2 months after), even when incentives are no longer offered [40].

### Component C: Parental/guardian engagement

According to current evidence, school-based interventions directly engaging parents are more effective than indirect strategies such as intervention-related newsletters [41]. Schools were encouraged to share feedback on students’ lifestyle behaviours with parents for this component. After completing all five teaching lessons, teachers shared the lesson video links with parents through the parent communication application. This serves to inform parents of their children’s lifestyle behavioural statuses and the health education concepts taught during the lessons and garner their support for their children’s participation in the intervention. As previously mentioned, a proportion of home activities were designed to encourage parental/family involvement so that children make behavioural changes with the support of at least one family member. Additionally, children were required to seek acknowledgement from their parents upon completing various activities, allowing parents to be aware of their children’s tasks and provide the necessary support.

#### Component D: Optimise school environment

There is strong evidence to demonstrate that intervening through education and environmental changes on both dietary and movement behaviours would enable sustainable and long-term behaviour change [42]. Hence, we planned to enhance children’s affective attitudes towards fruits and vegetables and reduce sedentary time by gamifying healthy eating and experiential learning through school-level-wide activities [34, 43]. With the help of the school’s Parent Support Group (PSG) and in collaboration with the Singapore Health Promotion Board, mini-games with different themes (e.g. guessing the fruit and vegetables through touch and smell, activity ideas/competition for breaking up sitting time, and a healthy lifestyle quiz) were conducted over at least two 30-min recess breaks during the intervention period. Students were awarded small tokens for completing the games.

Concomitantly, we worked with canteen vendors to develop practical and economical solutions to optimise the school food environment and reinforce the value of the current Healthy School Meals Programme (HSMP) [44]. For example, using choice architecture, such as the placement of foods and posters as cues, to remind students to ask for vegetables and take a portion of fruit. Needs assessments, through interviews, were conducted before the intervention commenced in both schools to help decide on practical solutions to optimise the canteen environment.

### Phase 2: Feasibility of PEDAL components A and B

#### Objectives

The objectives of this phase were to examine the feasibility of implementing components A and B of PEDAL and explore the experiences of ideation to confirm the intervention’s programme theory. Both qualitative and quantitative methods were used for this study. The findings from this phase informed the refinement of these two components and the evaluation tools used in Phase 3.

#### Key measures

##### Feasibility

Data were collected to assess five feasibility dimensions delineated by Gadke et al. [45]: recruitment capability, data collection procedures, social validity, practicality, and implementation. The recruitment capability dimension assesses the capability of successfully recruiting study participants in our study. Data collection procedures examine the appropriateness of data collection procedures and tools. Social validity assesses participants’ acceptability and satisfaction with the intervention. Practicality examines whether it is practical to implement the intervention with the available resources, time, training, and materials. Lastly, the implementation dimension examines the implementation fidelity. Progression criteria for each feasibility dimension were also pre-determined, guiding the decision and actions from Phases 2 to 3. Details of the feasibility dimensions and the progression criteria are shown in Table 3.

**Table 3 Tab3:** Feasibility dimensions, questions, measures and progression criteria for Phases 2 and 3^a^

Feasibility dimension	Research questions	Measure(s)	Progression criteria
Recruitment capability	Can participants who will benefit from and who will implement intervention be identified?	• Recruitment and participation rates of students and teachers • Recruitment rates of canteen vendors^a^	• ≥ 50% consent rates • ≥ 50% of consented participants attended the lessons • ≥ 50% consent rates from canteen vendors^a^
Data collection procedures	Are data collection procedures and outcome measures appropriate and sensitive to change?	• Survey completion rates among students and teachers • Descriptive analysis of scores from outcome measures • Survey completion rates among parents	• ≥ 50% of consented participants completed the survey • Survey questions and scales are appropriate without a ceiling effect • ≥ 50% of consented parents completed the survey
Social validity	Do participants perceive the intervention as appropriate, reasonable, fair, and potentially effective?	• Post-intervention feedback surveys from teachers and students • Post-intervention FGDs with students and teachers • Post-intervention interviews with canteen vendors^a^	• ≥ 75% satisfaction from student’s and teacher’s feedback surveys • Positive experiences from students, teachers, and canteen vendors^a^ • Positive experiences from canteen vendors^a^
Practicality	Can the intervention be implemented with available resources, time, training, and materials?	• Post-intervention FGDs with students and teachers • Post-intervention interviews with canteen vendors^a^ • Number of parent volunteers participated in canteen activities^a^	• Good feedback on the resources provided • Low level of perceived barriers on implementation from teachers and canteen vendors^a^ • At least 5 parent volunteers participated in the canteen activities^a^
Implementation	Are teachers able to implement the intervention with fidelity (as intended by the research team)? Are the canteen posters still in place by the end of the intervention?^a^	• Teacher-reported implementation checklist • Class observations^a^ • Canteen environmental scans^a^	• ≥ 75% fidelity among teachers, based on the checklist • ≥ 75% fidelity among teachers, based on class observations^a^ • ≥ 75% of the posters are still in place at the end of the intervention^a^
Potential Effectiveness of the whole PEDAL intervention^a^	Is there preliminary evidence of potential for bringing about positive change? What influenced the change (or no change) among the students?^a^	• Student outcome data^a^ • Canteen environmental scans ^a^ • Post-intervention interviews with students and teachers^a^ • Post-intervention interviews with canteen vendors^a^	• Improvements in fruit and vegetable intakes^a^ • Improvements in MVPA min/day^a^ • Reduction in screen time min/day^a^ • Improvements in ideation factors^a^ • Improvements in student’s health-related quality of life^a^ • Perceived improvements in behaviour and increased motivation for behaviour change^a^

^a^Additional items measured in Phase 3

##### Exploring ideation on healthy eating and physical activity

To confirm the feasibility of the programme theory, ideation on healthy eating and physical activity was explored using qualitative methods. Focus group discussions (FGDs) were conducted at the end of the intervention with students who participated and teachers who delivered the lessons. During the FGD, ideation factors that drive or impede healthy eating and physical activity among children and how components A and B influenced these ideation factors were explored. The findings from this will also inform the appropriateness of measuring the ideation variables in the questionnaire.

#### Setting and participants

Upon completion of the intervention prototype, two co-educational public schools in Singapore were recruited by convenience sampling to implement components A and B (health education lessons and home activities) of PEDAL. Co-educational public schools were selected as these were the most common type of primary schools in Singapore. The participants were students from the Primary 5 level, typically aged between 10 and 11 years old, from each school. This age group was chosen based on previous research that found that children aged 10 and above were capable of independently recalling and reporting their past activities [13, 46]. Two schools were selected for the pilot test as the required sample size to establish feasibility was calculated to be 385. This was calculated using a confidence interval (CI) approach [47], with a 95% CI, a margin of error of 0.05, and an expected completion rate of 50% based on our previous experience conducting research studies in primary school. Given that a primary school typically consists of six to eight classes of 40 students per level, the recruitment of two schools will meet the required sample size calculated. As the intervention posed minimal risk and was conducted as part of the school's Physical and Health Education curriculum, all Primary 5 students in the two selected schools were eligible to participate.

Both components, A and B, were delivered by each school’s Primary 5 Physical Education (PE) teachers. Training and lesson materials (e.g. slides, videos, home activity instructions, activity booklets for students, and teacher’s guide) were provided by the research team to the PE teachers before the intervention commenced. PE teachers from each school were given 8 weeks to complete the delivery of all the lessons and activities during the weekly 30-min health education lessons. Consent was obtained from teachers for delivering the intervention and parents regarding data collection from their children. Students whose parents or guardians did not provide consent for data collection were allowed to attend the lesson but were not included in the data collection.

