#### Setting and participants

The setting, selection of schools, and participants for this pilot study followed the same procedures as Phase 2. However, two other schools were approached to participate in this study. The ideal number of participants for this phase was 385 students, following the same calculation in Phase 2.

Based on the feedback from Phase 2, more time was needed to complete the series of health education lessons in addition to the scheduled physical and health education lessons. Therefore, the schools in this pilot study were given 12 weeks to complete all the lessons and activities. Like Phase 2, consent was obtained from teachers for delivering the intervention and parents regarding data collection from their children. Students whose parents or guardians did not provide consent for data collection were allowed to attend the lesson without any data collected from them.

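### The ±5-point margin behind n = 385 assumes independent students, but whole year groups come from two convenience-chosen schools, so at 385 students it is too narrow for any positive intra-class correlation

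*Protocol article*

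**What the plan says.** In the protocol article, Phase 2, Setting and participants, "the required sample size to establish feasibility was calculated to be 385". The basis is a confidence-interval approach "with a 95% CI, a margin of error of 0.05, and an expected completion rate of 50" per cent. The same paragraph fills that number with whole year groups: "two co-educational public schools in Singapore were recruited by convenience sampling", "a primary school typically consists of six to eight classes of 40 students per level", and every Primary 5 student in the two schools was eligible. The lessons were given by each school's own PE teachers.

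Phase 3 used two other schools, selected in the same way, and its Setting and participants section carries the number over: "The ideal number of participants for this phase was 385 students, following the same calculation in Phase 2".

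Table 3 sets the progression criteria that these rates are read against. They include "≥ 50% consent rates", at least 50% of consented participants attending lessons and completing the survey, and at least 75% satisfaction. No ICC, design effect or other allowance for clustering appears in the article. The Discussion concedes that two schools limit generalisability and that there is no comparison group. It does not say that the margin behind 385 is affected.

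**The concern.** The formula that yields 385 treats each student's response as independent of every other's. Students who share a class, a PE teacher and a school are likely to resemble one another in whether they attend, complete a survey or report satisfaction. If they do, 385 students carry less information than 385 independent ones, and the margin given as the reason for the sample size is not the margin the design delivers.

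The rates feed the progression criteria in Table 3, and the Phase 3 rates inform a definitive trial in other schools. A planner who takes ±5 points at face value would credit them with more precision than they have.

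**Working it through.** **Inputs from the article.** 95% confidence, margin d = 0.05, expected rate p = 0.50, n = 385, two schools, six to eight classes of 40 per school. This gives 2 × 6 = 12 to 2 × 8 = 16 classes, and 12 × 40 = 480 to 16 × 40 = 640 eligible students.

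**Input not in the article.** The ICC. All values below are assumptions, shown as a range.

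**Step 1: reproduce 385.** n = z² p(1−p)/d² = 1.96² × 0.25/0.05² = 384.15 to 384.16 (depending on the rounding of z), rounded up to 385. The match is exact, so nothing was added for clustering.

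**Step 2: allow for clustering.** Design effect DE = 1 + (m − 1) × ICC, with m students per cluster. Half-width = 1.96 × √(0.25 × DE/n).

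**Step 3: rates based on 385 students, clustering by class.** With 16 classes, m = 385/16 ≈ 24.1.

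| Class ICC (assumed) | DE | Effective n | Margin (points) |
|---|---|---|---|
| 0.01 | 1.23 | 313 | ±5.5 |
| 0.02 | 1.46 | 263 | ±6.0 |
| 0.05 | 2.15 | 179 | ±7.3 |
| 0.10 | 3.31 | 116 | ±9.1 |

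With 12 classes (m ≈ 32.1) the same four ICCs give ±5.7, ±6.4, ±8.0 and ±10.1.

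**Step 4: the consent rate.** Its denominator is all eligible students, so n = 480 to 640 and m = 40.

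| Class ICC (assumed) | DE | Margin, n = 480 | Margin, n = 640 |
|---|---|---|---|
| 0.01 | 1.39 | ±5.3 | ±4.6 |
| 0.02 | 1.78 | ±6.0 | ±5.2 |
| 0.05 | 2.95 | ±7.7 | ±6.7 |
| 0.10 | 4.90 | ±9.9 | ±8.6 |

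The larger denominator absorbs a small class ICC but not a moderate one.

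**Step 5: clustering by school.** With two schools and 385 students, m = 192.5. A school ICC of 0.01 gives DE = 1 + 191.5 × 0.01 = 2.92 and ±8.5 points. A school ICC of 0.02 gives DE = 4.83 and ±11.0. As the number of students per school grows, the half-width tends to 1.96 × √(0.25 × ICC/2), which is ±6.9 at ICC 0.01. Setting this floor to 0.05 gives ICC = 2 × (0.05/1.96)²/0.25 ≈ 0.005. Above that value, no number of students in two schools reaches ±5. Two schools leave 1 degree of freedom, so the study cannot usefully estimate this component.

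**Step 6: a rate other than 50%.** At 75% (the satisfaction criterion) and 385 students, the independent-student margin is 1.96 × √(0.1875/385) = ±4.3. With about 24 per class and class ICC 0.01 to 0.10 it becomes ±4.8 (DE 1.23) to ±7.9 (DE 3.31).

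**The case against.** The strongest reply is that little turns on this margin. The Data analysis sections give descriptive statistics for the feasibility rates, and Table 3 compares observed values with thresholds. No rule uses a confidence interval, and progression also rests on fidelity and qualitative evidence. Phase 3 calls 385 an ideal number, the Discussion already warns about two schools, and p = 0.50 is the worst case for a proportion. Clustered intervals may also sit in an analysis plan that is not shown. All of this stands and limits the consequence. It does not make the stated margin right: the article chose a precision argument for 385, and the Discussion concedes generalisability, not precision.

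A second reply is that the two schools' own students are the target population. A finite-population correction at 385 of 480 to 640 would then give about ±2.2 to ±3.2 points. But the Phase 3 criteria govern progression to a future definitive trial, so the rates are meant to apply beyond these schools.

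A reader might go further than the article allows in four ways:

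- *That the rates are far less precise than stated.* The size rests on assumed ICCs. At class ICC 0.01 the loss is about half a point, and for consent on 640 students the margin stays below ±5.
- *That consent and surveys cluster because class teachers handle them.* The text says that parents gave consent for data collection and PE teachers delivered lessons. It does not say who handled forms or surveys.
- *That a 50% expected rate meeting a 50% threshold belongs to this fault.* A true rate on the threshold makes the observed result uncertain with or without clustering.
- *That 385 is miscalculated.* The sum is correct; the independence assumption behind it does not fit the design.

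**Conclusion.** The point holds in a limited form. The article's ±5 points is a property of 385 independent students, and neither phase has such a sample. At 385 students and a 50% rate the direction is certain for any positive ICC. The size is not known: it runs from slight (±5.5) to nearly double (±9.1) over class ICCs of 0.01 to 0.10, and a school ICC as small as 0.01 to 0.02 would give ±8.5 to ±11.0. The consent rate is less affected at a low class ICC because its denominator is larger. These figures rest on assumed ICCs, roughly equal cluster sizes and the article's typical class numbers. Convenience selection of schools adds a possible bias that no interval measures. No stated decision rule changes, so this is a correction to stated precision and reporting, not a flaw that undermines the feasibility study.

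**What to change.** Keep the two schools per phase and the progression thresholds.

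1. In the sample-size text, or in the results papers that rely on it, say that ±5 points holds only for independent students. Give the range with the ICC marked as an assumption: about ±5.5 to ±9.1 points at 385 students for class ICC 0.01 to 0.10, and the separate figures for consent on 480 to 640 eligible students.
2. Report consent, completion and satisfaction rates by school, with class-clustered 95% confidence intervals that use a small-sample correction for 12 to 16 classes, next to the 50% and 75% criteria.
3. State that these intervals do not capture school-to-school variation (two schools, 1 degree of freedom) or bias from convenience selection.

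The cost is a less favourable stated precision and slightly more analysis work. No enrolment is added. The Study status section says that the pilot intervention is complete and data analysis is underway, so the change can still be made in reporting.
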